### **9.3 Plasma Studies**

Baseline and post-treatment plasma will be collected to assess tumor burden dynamics using exploratory circulating biomarkers, as well as to evaluate germline mutations in circulating DNA that may correlate with clinical benefit. Whole blood (up to 20 ml) will be collected at the designated time points in a 10 ml plasma preparation tubes with EDTA (PPT, BD Vacutainer, Franklin Lakes, NJ) and gently swirled to mix blood with EDTA. Within three hours of collection, the sample will be processed using standard procedures for plasma separation. Plasma will be divided into 1 ml aliquots and stored at -80°C. Pellets from this separation procedure will also be stored at -80°C. Please see the Laboratory Manual for further details.

**10. STUDY CALENDAR**

|                                              | Pre-Study | Week 1  |   | Weeks 2-3 |    | Week 4 |   | Weeks 5-7 |   | Week 8 |    | Weeks 9-11 |   | Week 12 |   | Weeks 13-15 |    | Week 16  |   | Off study  |
|----------------------------------------------|-----------|----------------------|---|-----------|----|--------|---|-----------|---|--------|----|------------|---|---------|---|-------------|----|-----------------------|---|-------------------------|
|                                              |           | M                    | W | F         | M  | W      | F | M         | W | F      | M  | W          | F | M       | W | F           | M  | W                     | F |                         |
| Visit Windows (days)             | -28 to -1 | +2                   | - | -         | +2 | -      | - | +2        | - | -      | +2 | -          | - | +2      | - | -           | +2 | -                     | - | +/- 7                   |
| Helixor® M                |           | X-----X              |   |           |    |        |   |           |   |        |    |            |   |         |   |             |    |                       |   |                         |
| Informed consent                             | X         |                      |   |           |    |        |   |           |   |        |    |            |   |         |   |             |    |                       |   |                         |
| Eligibility criteria                         | X         |                      |   |           |    |        |   |           |   |        |    |            |   |         |   |             |    |                       |   |                         |
| Demographics                                 | X         |                      |   |           |    |        |   |           |   |        |    |            |   |         |   |             |    |                       |   |                         |
| Medical and Cancer History                   | X         |                      |   |           |    |        |   |           |   |        |    |            |   |         |   |             |    |                       |   |                         |
| Con meds                                     | X         | X-----X              |   |           |    |        |   |           |   |        |    |            |   |         |   |             |    |                       |   |                         |
| Physical exam                    | X         | X                    |   |           |    |        |   |           |   | X      | X  |            |   | X       | X |             | X  | X                     |   | X                       |
| Vital signs                      | X         | X                    | X | X         | X  | X      | X | X         | X | X      | X  | X          | X | X       | X | X           | X  | X                     | X | X                       |
| Height                           | X         |                      |   |           |    |        |   |           |   |        |    |            |   |         |   |             |    |                       |   |                         |
| Weight                                       | X         | X                    |   |           |    |        |   |           |   | X      |    |            |   | X       |   |             | X  |                       |   | X                       |
| Performance status                           | X         | X                    |   |           |    |        |   |           |   | X      |    |            |   | X       |   |             | X  |                       |   | X                       |
| FACT-G Questionnaire                         |           | X                    |   |           |    |        |   |           |   | X      |    |            |   | X       |   |             | X  |                       |   | X                       |
| Hematology, Chemistry profile  | X         | X                    |   |           | X  |        |   | X         |   | X      |    |            |   | X       |   |             | X  |                       |   | X                       |
| Urinalysis & Microscopic Exam  | X         |                      |   |           |    |        |   |           |   |        |    |            |   |         |   |             |    |                       |   |                         |
| Pregnancy test                 | X         | X                    |   |           |    |        |   |           |   | X      |    |            |   |         |   |             |    | X                     |   |                         |
| Relevant Tumor Marker          | X         | X                    |   |           |    |        |   |           |   | X      |    |            |   | X       |   |             | X  |                       |   | X                       |
| Adverse event evaluation                     |           | X-----X              |   |           |    |        |   |           |   |        |    |            |   |         |   |             |    |                       |   |                         |
| Radiologic evaluation            | X         |                      |   |           |    |        |   |           |   | X      |    |            |   |         |   |             | X  |                       |   | X                       |

|                                     | Pre-Study | Week 1  |   |   | Weeks 2-3 |   |   | Week 4 |   |   | Weeks 5-7 |   |   | Week 8 |   |   | Weeks 9-11 |   |   | Week 12 |   |   | Weeks 13-15 |   |   | Week 16  |   |   | Off study  |
|-------------------------------------|-----------|----------------------|---|---|-----------|---|---|--------|---|---|-----------|---|---|--------|---|---|------------|---|---|---------|---|---|-------------|---|---|-----------------------|---|---|-------------------------|
|                                     |           | M                    | W | F | M         | W | F | M      | W | F | M         | W | F | M      | W | F | M          | W | F | M       | W | F | M           | W | F | M                     | W | F |                         |
| Tumor measurements      | X         |                      |   |   |           |   |   |        |   |   |           |   |   | X      |   |   |            |   |   |         |   |   |             |   | X |                       |   |   | X                       |
| PBMC (up to 32ml)                   |           | X                    |   |   |           |   |   | X      |   |   |           |   |   | X      |   |   |            |   |   | X       |   |   |             |   | X |                       |   |   | X                       |
| Serum (up to 10ml)                  |           | X                    |   |   |           |   |   | X      |   |   |           |   |   | X      |   |   |            |   |   | X       |   |   |             |   | X |                       |   |   | X                       |
| Whole Blood for Plasma (up to 20ml) |           | X                    |   |   |           |   |   | X      |   |   |           |   |   | X      |   |   |            |   |   | X       |   |   |             |   | X |                       |   |   | X                       |
| Archival Tissue        |           |                      |   |   |           |   |   |        |   |   |           |   |   |        |   |   |            |   |   |         |   |   |             |   |   |                       |   |   |                         |

X (optional with consent)

- 1: Longer delays to be approved by the IND sponsor. Patient-initiated dosing delays are not permitted during the first 8 weeks of treatment. Dosing delays due to clinic scheduling and holiday closures are permitted. Patients are allowed to move 1 treatment per week by 1 day (for example: MWF → TWF). Helixor® M infusions may not be given less than 24 hours apart.
- 2: Please see **Section 5.1** for dosing schedule according to the assigned dose level
- 3: Complete physical exam will be completed at baseline; focused physical examinations will be conducted thereafter. If study drug is held due to an AE, a physical exam is required before patient is allowed to restart drug.
- 4: Temperature, respiration rate, blood pressure, and pulse should be taken at the baseline and prior to each administration of Helixor® M. The patient must be observed in the clinic for at least 30 minutes after the lead in dose and the first dose of the assigned dose level. Height will be taken at or prior to screening only.
- 5: Clinical hematology: CBC with differential and platelet count; serum chemistry: sodium, potassium, chloride, bicarbonate, glucose, BUN, creatinine, ALT, AST, alkaline phosphatase, total bilirubin, total protein, albumin, and calcium. Clinically relevant tumor markers may be drawn by the clinician. For example, prostate cancer patients get monthly PSA values.
- 6: Bilirubin, blood, glucose, ketones, leukocytes, nitrite, pH, protein, and specific gravity
- 7: Pregnancy tests will be administered to WOCBP: Serum pregnancy test at baseline and urine pregnancy test thereafter.
- 8: Labs may be collected within a window of up to 3 days prior to dosing.
- 9: Radiologic evaluations (CT scan of the chest, abdomen, and pelvis or MRI if patient has contrast allergy) and tumor measurements (RECIST 1.1 and irRC) will be performed at baseline, week 8 (+/-7 days), and every 8 weeks (+/-7 days) thereafter. Off study scans only need to be completed if the off study visit occurs before the Week 8 scan; scans do not need to be repeated if one has been done within the past 6 weeks. Bone scans will also be performed if applicable.
- 10: Attempts to obtain surgical or biopsy archival tumor samples will be made for every subject who consents to the optional sample until the sample is obtained or documentation that the sample cannot be obtained. Detailed instructions for tissue collection, processing and shipment are provided in the

Protocol #: J1681, IRB00090991

Laboratory Manual.

- 11: For Cycle 1 Day 1 (50mg dose level) study procedures do not need to be repeated if they were conducted within 3 days of the pre-study evaluations.
- 12: Beyond Week 16, repeat the study assessments and evaluations detailed in Weeks 9-16 until one of the criteria from **Section 5.6** applies.
- 13: 28 days after their last dose of study drug or within 7 days prior to initiation of a new anti-cancer treatment, whichever comes first. Patients who have completed or discontinue from treatment should be contacted every six months (+/- 28 days) to monitor overall survival. Information regarding anti-cancer therapies after discontinuation from the study treatment will also be collected.

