## 11. MEASUREMENT OF EFFECT

Although response is not the primary endpoint of this trial, patients with measurable disease will be assessed by standard criteria. For the purposes of this study, patients should be evaluated at baseline, week 8, every 8 weeks thereafter, and at the off study visit (if the patient comes off study before week 8 or it has been more than 6 weeks since the last scan) with a CT with oral and IV contrast of the chest, abdomen and pelvis (or MRI if patient has contrast allergy). In addition a bone scan will be performed for prostate cancer patients at baseline and at study completion.

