Exploratory objectives will be to 1) to estimate PFS and TTP in patients treated with Helixor® M at MTD or maximum administered dose if no MTD is determined, and to measure tumor marker dynamics in patients receiving treatment, 2) collect peripheral blood mononuclear cells (PBMCs) and serum to explore potential therapeutic targets, biomarkers, and predictors of treatment response, 3) assess tumor burden dynamics using exploratory circulating biomarkers in serial collections of sera and plasma at baseline and throughout treatment, 4) collect pre and post-treatment whole blood to evaluate germline mutations in circulating DNA that may correlate with clinical benefit, and 5) determine changes in cytokine production by peripheral blood mononuclear cells (PBMC) as indicated by interleukin 2 [IL-2], interleukin 6 [IL-6], interleukin 8 [IL-8], interleukin 12 [IL-12], and interferon- gamma [IFN-γ]. PFS and TTP will be analyzed as time-to-event outcomes, for which we can estimate event-time distributions using the Kaplan-Meier method. PFS will be calculated as the time from start of treatment to time of progression per RECIST 1.1 and irRC or death, whichever occurs first. If the subject does not have a documented date of progression or death, PFS will be censored at the date of the last adequate assessment. Patients who start any subsequent anti-cancer therapy without a prior reported progression will be censored at the last evaluable tumor assessment prior to initiation of the subsequent anti-cancer therapy. TTP is the time from start of treatment to time of progression per RECIST 1.1 and irRC.

We will examine the correlation between potential therapeutic targets/biomarkers/predictors of treatment response and clinical endpoints. For time-to-event clinical endpoints, the potential predictors will be treated as covariates (time-varying or not) in Cox proportional-hazard models. For other clinical endpoints, we will use generalized estimating equations (GEE) to analyze the correlation between the potential predictors and clinical endpoints. Summary statistics and boxplots will be used to present the levels of potential predictors at each time point, assess tumor burden dynamics, compare pre and post-treatment germline mutations in circulating DNA, and examine the changes in cytokine production by PBMC.

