| * See RECIST 1.1 manuscript for further details on what is evidence of a new lesion.                                                                                                                                                                                                                                                            |                             |             |                  |                                                        |
| ** Only for non-randomized trials with response as primary endpoint.                                                                                                                                                                                                                                                                            |                             |             |                  |                                                        |
| *** In exceptional circumstances, unequivocal progression in non-target lesions may be accepted as disease progression.                                                                                                                                                                                                                         |                             |             |                  |                                                        |
| Note: Patients with a global deterioration of health status requiring discontinuation of treatment without objective evidence of disease progression at that time should be reported as “ symptomatic deterioration. ” Every effort should be made to document the objective progression even after discontinuation of treatment. |                             |             |                  |                                                        |

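### Calendar footnote 9 and Section 11 of the protocol give different off-study scan rules, so some progressions at exit may go undocumented in the exploratory TTP and PFS estimates

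*Protocol*

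**What the plan says.** Scans "will be performed at baseline, week 8 (+/-7 days), and every 8 weeks (+/-7 days) thereafter" (Section 10, footnote 9). The off-study column also carries a mark in both imaging rows, and two texts say when that scan is needed.

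- Section 10, footnote 9: "Off study scans only need to be completed if the off study visit occurs before the Week 8 scan". The same sentence continues after a semicolon: "scans do not need to be repeated if one has been done within the past 6 weeks".
- Section 11: at the off-study visit, "if the patient comes off study before week 8 or it has been more than 6 weeks since the last scan".

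The off-study visit takes place "28 days after their last dose of study drug or within 7 days prior to initiation of a new anti-cancer treatment, whichever comes first" (Section 10, footnote 13). Section 5.8 removes a patient from study once a Section 5.6 criterion applies, and footnote 12 continues the assessments past week 16 only until then. The off-study scan is therefore the last scheduled chance to document progression.

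Without documented progression or death, "PFS will be censored at the date of the last adequate assessment" (Section 13.3). A patient who starts another anti-cancer therapy first is censored at the last evaluable assessment before it. Section 11.1.4 counts death from any cause as a PFS event; Section 11.1.5 censors TTP at death. For patients who stop because of global deterioration, Appendix D asks: "Every effort should be made to document the objective progression even after discontinuation of treatment". PFS and TTP are exploratory (Section 1.3.1).

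**The concern.** The same patient can require a scan under one section and not under the other. A patient who leaves between scheduled scans because the disease is getting worse is likely to have unrecorded progression. If the off-study scan is skipped, no objective progression is recorded, the patient is censored at the previous scan, and the assessment cannot be recovered later. That works against the request in Appendix D.

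What is at stake is the Kaplan-Meier description of TTP and PFS at the dose taken into the expansion phase, where 16 patients are planned (Section 13.2). One lost progression there is 1/16, about 6% of the group.

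**Working it through.** **The two rules side by side, read literally**

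| Situation at the off-study visit | Section 11 | Footnote 9 |
|---|---|---|
| Before week 8, last scan over 6 weeks old | scan | scan |
| Before week 8, last scan under 6 weeks old | scan | excused by the second clause |
| Past the Week 8 scan, last scan over 6 weeks old | scan | not required |
| Past the Week 8 scan, last scan within 6 weeks | no scan | no scan |

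Rows 2 and 3 conflict.

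*Row 3, example.* Scan at week 8, last dose at week 14, visit at week 18. Scan age is 18 − 8 = 10 weeks. Section 11 requires a scan; footnote 9 does not. Without the scan, and with no recorded death, PFS is censored at week 8.

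*Row 2, example.* Baseline scan the day before the first dose (Sunday), last dose on Friday of week 1, visit 28 days later. Scan age is 5 + 28 = 33 days, under 42. Section 11 requires a scan; footnote 9 excuses it.

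**How many exits row 3 covers**

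Inputs from the protocol: 8-week interval, 6-week limit, visit up to 28 days after the last dose. Assumption: stopping is uniform over the interval. With stopping *d* weeks after the last scan and a visit *v* weeks after stopping, Section 11 requires a scan when *d* + *v* > 6.

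- Visit at stopping (*v* = 0): *d* > 6, share (8 − 6)/8 = 25%.
- Visit 28 days later (*v* = 4): *d* > 2, share (8 − 2)/8 = 75%.

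Neither rule scans the rest.

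**Effect on the estimate**

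The protocol gives no PFS or TTP figure to reproduce, so the inputs below are assumptions. Deaths are not generated, so the results describe TTP. Only row 3 differs between the rules.

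*Set A:* exponential progression with median 8, 12 or 16 weeks; 20% to 40% of progressors leave between scans for deterioration; visit 4 weeks later. Hand check at median 12 weeks and 30%, with the patient leaving at progression: the probability of progressing after week 8 is 2^(−8/12) = 0.630. Given that, the probability of doing so within 2 weeks of a scan is (1 − 2^(−2/12))/(1 − 2^(−8/12)) = 0.295. Recorded progression is then

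- footnote 9: 1 − 0.3 × 0.630 = 0.811 (simulated 0.810);
- Section 11: 1 − 0.3 × 0.630 × 0.295 = 0.944 (simulated 0.943).

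The simulated 32-week estimates are 0.228 under footnote 9 and 0.189 under Section 11. Across the set the difference is 0.012 to 0.069.

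*Set B:* median 8, 16 or 24 weeks; other exits at 0.02 or 0.04 per week; 0% or 50% leaving for deterioration a mean of 3 weeks after progression; visit 0 or 4 weeks after stopping; 200,000 patients per setting. Selected results with a true median of 16 weeks:

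| Exit pattern | Visit lag | 32-week estimate, footnote 9 | Section 11 | Difference |
|---|---|---|---|---|
| Unrelated, 0.02 | 0 | 0.243 | 0.236 | 0.007 |
| Unrelated, 0.02 | 4 weeks | 0.242 | 0.239 | 0.003 |
| 50% linked, 0.02 | 0 | 0.336 | 0.295 | 0.041 |
| 50% linked, 0.02 | 4 weeks | 0.322 | 0.262 | 0.060 |
| 50% linked, 0.04 | 4 weeks | 0.302 | 0.239 | 0.063 |

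Across the three medians the difference is about 0.02 to 0.07 with linked exits and below 0.01 with unrelated exits. The direction is not uniform at other points. In the fourth row the 16-week estimate is lower under footnote 9 (0.524 against 0.538) while the median is longer (24.0 against 18.5 weeks). In the fifth row the median is shorter (16.0 against 17.1 weeks).

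**The case against.** The strongest reply is that footnote 9 should be read whole. Its second clause uses Section 11's own 6-week limit, and a reader could take it to imply a scan when the last one is older. On that reading row 3 disappears. This stands as a reason to call the footnote ambiguous, but not as a resolution. The clause is worded as a further waiver, it does not cancel the restriction to visits before the Week 8 scan, and it has its own use when the baseline scan is recent.

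A reader might infer more: that the protocol waives the off-study scan for everyone past week 8, and that PFS and TTP are therefore too long. The documents do not support this. The waiver follows from only one reading of the footnote, and Section 11 requires the scan. The bias needs exits linked to unseen progression. Patients who leave because a scan showed progression are unaffected, and those leaving after week 8 within 6 weeks of a scan go unscanned under Section 11 too. Section 5.7 keeps survival contact every six months, so later deaths still count as PFS events where no new therapy was started. That limits the effect on PFS more than on TTP.

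Size also matters. With 16 patients and an estimate near 0.2, the standard error is about √(0.2 × 0.8/16) = 0.10 before censoring, larger than any shift found above.

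**Conclusion.** The contradiction holds on the literal wording, for exits past the Week 8 scan with a scan over 6 weeks old and for exits before week 8 with a scan under 6 weeks old. In the first case, following footnote 9 may leave progression undocumented and move censoring back to the earlier scan.

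Under assumed inputs with exits linked to progression, the 32-week TTP estimate is about 0.01 to 0.07 higher under footnote 9 than under Section 11, and PFS is affected less. The difference is near zero if exits are unrelated, and no single direction can be claimed for the median. Only the 8-week interval, the 6-week limit and the 28-day visit come from the protocol; progression medians, exit rates and reasons for exit are assumptions.

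Severity is minor. The endpoints are exploratory and estimated without a test, and the primary objectives, safety and the MTD, do not depend on these scans.

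**What to change.** Reconcile footnote 9 and Section 11 into one rule. Amend footnote 9 so that it also calls for an off-study scan when the last scan is more than 6 weeks old at the off-study visit, as Section 11 already does. State in both places whether the within-6-weeks waiver applies to exits before week 8. Copying Section 11's rule while leaving the waiver untouched would keep the second conflict alive.

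The cost is a short edit to the footnote and a matching clause in Section 11. The 6-week change adds no procedure beyond what Section 11 already requires. Reported TTP and PFS may come out slightly shorter at later time points.
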